**Figure 1 figure1:**
[figure not shown]
Flowchart of the study design from enrollment to analysis. CHM: Chinese herbal medicine.

### Chemotherapy and CHM Administration Protocol

Upon the diagnosis of breast cancer in a patient, a clinical nurse manages the case. The questionnaire and blood collection before chemotherapy are represented by visit 1 (red arrow in Figure 2). The first 4 rounds of chemotherapy will be performed every 3 weeks, and visits 2-4 will be located in the second, third, and fifth rounds, respectively, 1 day before chemotherapy treatment. The following 12 rounds of chemotherapy will be performed every week, and visits 5-8 will be located in the first, fourth, seventh, and tenth rounds, respectively, 1 day before chemotherapy treatment. The patients will be followed up within 1 month after chemotherapy (Figure 2 and Table 2). Patients receiving CHM 3 times per day started the first round of chemotherapy.

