### Study Design

This study is a real-world pragmatic clinical trial conducted at the Hualien Tzu Chi Hospital in Taiwan. Patients with breast cancer scheduled to receive chemotherapy for their cancer treatment will be recruited as per the flowchart shown in Figure 1. Patients willing to receive CHM during chemotherapy are allocated to the CHM group, whereas those in the non-CHM group will not receive CHM.

To evaluate the effectiveness of CHM, the number of WBCs, the ANC, and the use of G-CSF in patients will be measured. The following questionnaires in Taiwanese will be used: (1) the Brief Fatigue Inventory—Taiwanese Version, (2) the World Health Organization Quality of Life-BREF, (3) the National Cancer Institute-Common Terminology Criteria for Adverse Events & Patient Reported Outcomes, and (4) the body constitution questionnaire. In addition, blood samples will be collected and analyzed for immune profiles and programmed cell death protein 1 (PD-1) expression. Generally, visit 1 represents the first collection of questionnaires and blood samples before the first chemotherapy session. Following the chemotherapy regimen, the first 4 rounds of chemotherapy will be performed every 3 weeks with 3 visits (visits 2-4). Subsequently, 12 rounds of chemotherapy will be performed once per week with another 4 visits (visits 5-8, 3 weeks per visit). Patients will be followed up within 1 month of undergoing chemotherapy. Patients in the CHM group will receive complementary CHM treatment after the first chemotherapy session.

The clinical data will be extracted from the medical history system. The questionnaires will be coded and transformed into numerical values (eg, 5=very satisfied or none, 4=satisfied or light, 3=no change or intermediate, 2=unsatisfied or severe, and 1=very unsatisfied or none) to facilitate statistical analysis. Immune profiles will be analyzed using flow cytometry. The data monitoring committee, clinical trial center of Hualien Tzu Chi Hospital, is independent from the funder and competing interests. The SPIRIT (Standard Protocol Items: Recommendation for Interventional Trials) 2013 checklist is provided in Multimedia Appendix 1 [20].

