**Figure 2 figure2:**

Chemotherapy, Chinese herbal medicine intervention, and data collection procedures. The questionnaire and blood collection before chemotherapy represent V1 (red arrow). The first 4 rounds of chemotherapy will be performed every 3 weeks (V2 to V4), 1 day before chemotherapy treatment. The subsequent 12 rounds of chemotherapy will be performed every week (V5 to V8), 1 day before chemotherapy treatment. The patients will be followed up (FU) after chemotherapy within 1 month. V: visit.

**Table 2 table2:** Recommended content for the schedule according to the SPIRIT (Standard Protocol Items: Recommendation for Interventional Trials) 2013 guidelines.

Time point		Enrollment	Allocation	Treatment									Follow-up
		Week 1	Week 0	Visit 1	Visit 2	Visit 3	Visit 4	Visit 5		Visit 6	Visit 7	Visit 8	

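### Visit 4 is tied to a fifth round that the four-round block does not have; counted across both blocks, that round is where Visit 5 already sits

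*Protocol article*

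**What the plan says.** The section Chemotherapy and CHM Administration Protocol sets out two blocks: "The first 4 rounds of chemotherapy will be performed every 3 weeks", and then "The following 12 rounds of chemotherapy will be performed every week". It attaches visits to rounds in both. For the first block, "visits 2-4 will be located in the second, third, and fifth rounds, respectively, 1 day before chemotherapy treatment". For the second, "visits 5-8 will be located in the first, fourth, seventh, and tenth rounds, respectively, 1 day before chemotherapy treatment".

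Three other places describe the same schedule:

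- Study Design says that "the first 4 rounds of chemotherapy will be performed every 3 weeks with 3 visits (visits 2-4"), followed by "12 rounds of chemotherapy will be performed once per week with another 4 visits (visits 5-8, 3 weeks per visit"). It also fixes the baseline: "visit 1 represents the first collection of questionnaires and blood samples before the first chemotherapy session".
- The Figure 2 legend makes the same split: "The first 4 rounds of chemotherapy will be performed every 3 weeks (V2 to V4), 1 day before chemotherapy treatment", with Visits 5 to 8 in the weekly block.
- Table 2 gives Visit 4 and Visit 5 separate columns. Blood counts, G-CSF use, questionnaires, immune cell profile and adverse events are listed by visit.

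**The concern.** The paragraph on chemotherapy and CHM administration is the only place in the article that says which round each visit belongs to, and its entry for Visit 4 cannot be carried out as a separate visit. The block it describes has four rounds, so a fifth round is either absent or belongs to the next block, where Visit 5 already is.

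This matters because the primary outcome is measured at these visits. It consists of flow-cytometry cell counts and PD-1 expression in fresh blood that must be processed within 24 hours, so a draw that was not taken cannot be recovered later. The Statistical Analysis section treats primary and secondary outcomes as repeated measurements. It compares visits within each group by the Friedman test or repeated measures ANOVA, and compares the groups by generalized estimating equations or repeated measures ANOVA. If the sentence is followed literally, one planned time point in that analysis has no sampling day of its own. Recruitment began in September 2021, so samples labelled Visit 4 may already exist.

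**Working it through.** No formula in the plan produces the visit dates, so the check rebuilds the calendar from the stated rounds.

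**Inputs**

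- First block: 4 rounds, 3 weeks apart (Chemotherapy and CHM Administration Protocol).
- Second block: 12 rounds, 1 week apart (same section).
- Visits 2, 3 and 4 at rounds 2, 3 and 5; Visits 5 to 8 at weekly rounds 1, 4, 7 and 10; each one day before treatment (same section).
- Visit 1 before the first session (Study Design), taken here as one day before.
- Gap *g* between round 4 and the first weekly round: not stated. Assumed 21 days, with 7 to 28 days as the range.

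**Reading A: fifth counted within the block.** The block has rounds 1 to 4 only. Visit 4 has no date.

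**Reading B: fifth counted across both blocks.** Let round 1 be day 0.

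- Rounds 1 to 4 fall on days 0, 21, 42 and 63.
- Weekly round *k* falls on day 63 + *g* + 7(*k* − 1).
- Overall round 5 is weekly round 1, on day 63 + *g*.
- Each visit is the round day minus 1.

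| Visit | Round | Day, general | Day, *g* = 21 |
|---|---|---|---|
| 1 | 1 | −1 | −1 |
| 2 | 2 | 20 | 20 |
| 3 | 3 | 41 | 41 |
| 4 | 5 overall | 62 + *g* | 83 |
| 5 | weekly 1 | 62 + *g* | 83 |
| 6 | weekly 4 | 83 + *g* | 104 |
| 7 | weekly 7 | 104 + *g* | 125 |
| 8 | weekly 10 | 125 + *g* | 146 |

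**Results under reading B**

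- Visit 5 minus Visit 4 = (62 + *g*) − (62 + *g*) = 0 days. The gap cancels, so the coincidence does not depend on it.
- Distinct days: seven for Visits 1-8, or six for the seven visits after baseline.
- Visit 3 to Visit 4 = (62 + *g*) − 41 = 21 + *g*, which is 28, 35, 42 and 49 days for *g* = 7, 14, 21 and 28.
- The day before round 4 is day 62. No study visit falls on it.

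**Comparison with the other descriptions.** Visits 5 to 8 come out 21 days apart, as Study Design says, so the weekly half of the schedule is consistent. Visit 4 is the only misfit: Study Design and the Figure 2 legend put it within the first four rounds, and Table 2 keeps it apart from Visit 5.

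**Illustration only.** If Visit 4 preceded round 4, it would fall on day 62. All eight visits would be distinct, and at *g* = 21 they would be evenly spaced at 21 days. The article does not say that this was meant.

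**The case against.** The strongest reply is that this is a slip of one word. The next sentence numbers the weekly rounds within their own block. By that convention fifth names a non-existent round, which points to a wording error and not to a planned double visit. Study Design, the Figure 2 legend and Table 2 all describe distinct visits, and the Figure 2 graphic, not available here, may show the intended day. The article is also a condensed account of a single-center study, and staff may work from a fuller protocol. All of this is fair, and it rules out presenting the coincidence as the only reading. It does not rescue the sentence: neither way of counting gives a usable Visit 4, and a correct graphic would simply be one more place that the text contradicts.

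A reader might infer more than the documents support:

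- *That blood counts before round 4 are never taken.* Study Design extracts clinical data from the medical history system, and Safety Assessments promises continuous monitoring of blood. Routine counts may well exist. What is in doubt is the scheduled study collection, above all the immune profile and questionnaires.
- *That adverse events go unrecorded.* Safety Assessments records them throughout the study, so their capture does not hang on the date of Visit 4.
- *That one sample will enter the model under two labels.* Nothing in the article says so. It is only a possibility if the sentence is followed literally and the labels are taken at face value.
- *That there is a fixed 6-week hole in sampling.* The 42 days depend on an assumed 21-day gap between blocks.

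**Conclusion.** The sentence is wrong as written. It places Visit 4 at a round that either does not exist or is already Visit 5's, and it contradicts Study Design, the Figure 2 legend and Table 2. This conclusion needs no assumption about the calendar.

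On the overall count, one of eight planned sampling days is lost (one of seven after baseline), and no scheduled study visit precedes round 4. The length of the interval between Visits 3 and 4 does depend on the assumed gap. Whether any patient was actually sampled on the wrong day cannot be judged from the article.

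The error does not touch the sample size. It bears on which time points the repeated-measures analysis of the primary outcome really contains, and it is worth correcting because the correction is cheap and lost fresh-blood samples cannot be replaced.

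**What to change.** Reconcile the round named for Visit 4 in Chemotherapy and CHM Administration Protocol with Study Design, the Figure 2 legend and Table 2, so that each of Visits 1 to 8 maps to one distinct sampling day. State the interval between round 4 and the first weekly round as scheduled, so that the calendar can be read without assumption.

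For patients already enrolled, check the actual date and chemotherapy round of every sample labelled Visit 4 or Visit 5. Use these to assign the sample to its time point in the repeated-measures analysis, so that no sample is counted under two visits and any missing Visit 4 is recorded as missing.

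The cost is a one-line correction to the schedule and a check of dates on the case report form and in the medical record. Neither treatment nor sample size changes.

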**Figure 2 figure2:**

Chemotherapy, Chinese herbal medicine intervention, and data collection procedures. The questionnaire and blood collection before chemotherapy represent V1 (red arrow). The first 4 rounds of chemotherapy will be performed every 3 weeks (V2 to V4), 1 day before chemotherapy treatment. The subsequent 12 rounds of chemotherapy will be performed every week (V5 to V8), 1 day before chemotherapy treatment. The patients will be followed up (FU) after chemotherapy within 1 month. V: visit.

**Table 2 table2:** Recommended content for the schedule according to the SPIRIT (Standard Protocol Items: Recommendation for Interventional Trials) 2013 guidelines.

Time point		Enrollment	Allocation	Treatment									Follow-up
		Week 1	Week 0	Visit 1	Visit 2	Visit 3	Visit 4	Visit 5		Visit 6	Visit 7	Visit 8	
**Enrollment**													
	Eligibility screen	✓											
	Informed consent	✓											
	Allocation		✓										
**Intervention**													
	Control group			✓	✓	✓	✓	✓	✓	✓	✓	✓	
	CHM^a^ group			✓	✓	✓	✓	✓	✓	✓	✓	✓	
**Assessment**													
	ANC^b^ or WBC^c^			✓	✓	✓	✓	✓	✓	✓	✓	✓	
	Frequency of G-CSF^d^ injection			✓	✓	✓	✓	✓	✓	✓	✓	✓	
	Questionnaire			✓	✓	✓	✓	✓	✓	✓	✓	✓	
	Immune cell profile			✓	✓	✓	✓	✓	✓	✓	✓	✓	
	Adverse events			✓	✓	✓	✓	✓	✓	✓	✓	✓	

^a^CHM: Chinese herbal medicine.

^b^ANC: absolute neutrophil count.

^c^WBC: white blood cell.

^d^G-CSF: granulocyte colony-stimulating factor.

### Primary Outcome

The primary outcome used in this study is the number of immune cells, including CD4+ and CD8+ T cells (under CD45+ and CD3+ population), CD56+ NK cells (under CD45+ population), CD19+ B cells (under CD45+ population), CD14+ monocytes (under CD45+ population), and CD11c dendritic cells (under CD45+ population), as well as PD-1 expression levels in these cells. For NK cells, the expression of NKG2D will be also confirmed. The analytic panels used are listed in Table 3.

**Table 3 table3:** Antibodies used for flow cytometry analysis^a^.

Cells or conjugate	FITC^b^	PE^c^	APC^d^	APC-Cy7^e^	PE-Cy7^f^
T cells	CD45^g^	CD4	CD8	CD3	PD-1^h^
B and NK^i^ cells	CD45	NKG2D	CD56	CD19	PD-1
Monocytes or DCs^j^	CD45	CD14	CD11c	—^k^	PD-1

^a^CD45 (304006), CD4 (317410), CD8 (301014), CD3 (344818), and CD19 (302218) were purchased from Biolegend. PD-1 (25-9969-42), CD56 (17-0567-42), NKG2D (12-5878-42), CD14 (12-0149-42), and CD11c (17-0114-82) were purchased from eBioscience.

^b^FITC: fluorescein isothiocyanate.

^c^PE: phycoerythrin.

^d^APC: allophycocyanin.

^e^APC-Cy7: allophycocyanin-cyanine 7.

^f^PE-Cy7: phycoerythrin-cyanine 7.

^g^CD: cluster of differentiation.

^h^PD-1: programmed cell death protein 1.

^i^NK: natural killer.

^j^DC: dendritic cell.

^k^Not available.

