### Sample Size Estimation

The sample size calculation was based on the mean and SD of the amount of CD4+ between control and treatment groups based on the published literature [19]. By setting the effect size as 0.5, the sample size of each group was estimated as 64 to achieve a power of 0.80 at a significance level of .05 using G*Power software (version 3.1; Heinrich-Heine-Universität Düsseldorf). After accounting for an anticipated dropout rate of 10%, the final sample size was determined to be 70 in each group.

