### Statistical Analysis

All statistical analyses will be performed using the SPSS software (version 13.0; IBM Corp) or SAS software (version 9.4; SAS Institute Inc). Continuous variables will be reported as mean and SD, whereas categorical variables will be reported as frequencies and percentages. The Shapiro-Wilk test will be used to analyze the normality of baseline characteristics and outcome variables. The Mann-Whitney *U* test will be used to compare nonnormally distributed continuous data, and the 2-tailed *t* test will be used to compare normally distributed continuous data. The chi-square test will be used to compare categorical data between the groups. Both primary and secondary outcomes involve repeated measurement data. The Friedman test and repeated measures ANOVA will be used to compare the differences between every visit in each group in nonparametric and parametric data, respectively. In addition, we will use generalized estimating equations or repeated measures ANOVA to compare the differences between the 2 groups. We will evaluate the risks of each clinical characteristic by the multivariate logistic regression analysis and adjust the age and other factors or characteristics that may have bias in the analysis. We set *P*<.05 as a significant difference. All data will be recorded in a case report form.

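### The primary outcome comprises 12 to 13 immune measures judged at one unadjusted .05 threshold, while the sample size rests on a single CD4+ comparison

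*Protocol article*

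**What the plan says.** Three sections of the protocol article bear on this point.

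- **Primary Outcome**: "The primary outcome used in this study is the number of immune cells, including CD4+ and CD8+ T cells". The same sentence adds NK cells, B cells, monocytes and dendritic cells, then "as well as PD-1 expression levels in these cells". A separate sentence says: "For NK cells, the expression of NKG2D will be also confirmed".
- **Sample Size Estimation**: "The sample size calculation was based on the mean and SD of the amount of CD4+ between control and treatment groups". The assumed effect size is 0.5 and the target power 0.80, which gives 64 patients per group. Alpha is taken as .05 and is not divided. After an allowance for 10% dropout the target is 70 per group.
- **Statistical Analysis**: P<.05 is set "as a significant difference", with no distinction between primary and secondary outcomes. Both are described as repeated measurements, and the groups are to be compared by generalized estimating equations or repeated measures ANOVA.

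None of these sections ranks the immune measures or says whether one significant measure, or all of them, would make the primary result positive.

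**The concern.** The sample size section treats the primary question as one test on CD4+. The outcome section makes it a family of 12 to 13 measures, and the analysis section applies the same .05 to each. Read together, they allow any one marker below .05 to be reported as a positive primary result. The 5% error rate used to size the trial would then not be the error rate of its primary conclusion.

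The setting raises the stakes. Groups are formed by patients' willingness to take CHM (Study Design), treatment is open-label (Conclusions), and the article concedes that internal validity is compromised (Strengths and Limitations). A chance finding on one of many markers would be hard to recognise as such.

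**Working it through.** **Inputs.** From Primary Outcome: 6 cell numbers + 6 PD-1 levels + 1 NKG2D = 13 measures, or 12 without NKG2D. From Sample Size Estimation: d = 0.5, alpha .05, power 0.80, 64 per group, 10% dropout, 70 per group. From Statistical Analysis: threshold .05 and a 2-tailed t test. Assumed, because the document gives no figures: the correlations between measures, and d = 0.5 for measures other than CD4+.

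**1. The plan's own figure.** For a two-sample t test, two-sided .05, d = 0.5 and power 0.80, the normal approximation gives n = 2(1.960 + 0.842)²/0.5² = 62.8, so 63. The noncentral t gives 63.77, so 64 per group, as stated. Power at 64 per group is 80.1%. At 63 per group (70 × 0.90) it is 79.5%. The calculation is sound for one comparison.

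**2. Chance of at least one false positive, independent tests.** The formula is 1 − 0.95^m.
- m = 13: 1 − 0.95^13 = 48.7%
- m = 12: 1 − 0.95^12 = 46.0%
- m = 6 (cell numbers only): 1 − 0.95^6 = 26.5%

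**3. The same chance with correlated tests.** For equally correlated normal test statistics with correlation ρ and c = 1.96, the chance is 1 − ∫ [Φ((c − √ρ·u)/√(1−ρ)) − Φ((−c − √ρ·u)/√(1−ρ))]^m φ(u) du.

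| Assumed ρ | 13 measures | 12 measures | 6 cell numbers |
|---|---|---|---|
| 0 | 48.7% | 46.0% | 26.5% |
| 0.3 | 41.8% | 39.7% | 24.1% |
| 0.5 | 33.4% | 31.9% | 20.7% |
| 0.7 | 24.1% | 23.2% | 16.4% |
| 0.9 | 13.8% | 13.5% | 10.8% |

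Every entry is more than twice 5%.

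**4. Power if alpha were shared.** Bonferroni over 13 gives .05/13 = .00385. By the noncentral t with d = 0.5, power is 44.8% at 63 per group and 45.7% at 64. Reaching 80% would take 114 per group before dropout. Over 12 measures (.00417) the figures are 45.8%, 46.7% and 112.

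**5. Power if all measures had to succeed.** With 80% power for each of 13 measures, joint power is 0.8^13 = 5.5% if independent, 34% at ρ = 0.5 and 63% at ρ = 0.9.

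Steps 2 and 3 describe the plan as written if any significant measure counts. Steps 4 and 5 describe rules that the document does not state.

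**The case against.** **Power.** A reader might infer that neither the 5% error rate nor the 80% power holds. The document does not support that, because the two failures belong to different rules. At unadjusted .05 the CD4+ comparison has the stated 80.1% power, and what fails is the error rate across the family. Power drops to about 45% only if alpha is divided over 13, and then the error rate is controlled. This part of the objection stands in full.

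**Visits.** A reader might also infer that the error multiplies over visits. Statistical Analysis assigns visit-to-visit comparisons to within-group tests. For the comparison between groups it names models that can pool visits. Between-group tests at each visit are not explicitly planned, so none are counted here.

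**The count and the correlations.** The NKG2D sentence can be read as a check rather than a test, so 12 is as defensible as 13. The correlations are assumed, and markers measured in the same blood sample may be strongly related. Both points widen the range, but neither brings the error rate near 5%.

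**Single-test validity.** With allocation by willingness, each test may itself be biased. The percentages therefore show what multiplicity alone contributes and are not the trial's real false-positive rate.

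**Unseen documents.** A full protocol or analysis plan could hold a multiplicity procedure, and its absence from the article is no finding. The mismatch is between things the article does state: a multi-part primary outcome, one threshold, and a size for one measure. Sharing alpha in a later document would contradict the unadjusted .05 in Sample Size Estimation.

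**Conclusion.** The point holds as a mismatch between three stated choices. If any significant measure counts as a positive primary result, the chance of at least one false positive over 13 measures runs from 48.7% (independent) to 13.8% (assumed correlation 0.9). For 12 measures the range is 46.0% to 13.5%. These figures assume equal correlations, a valid single test for each measure and no true effect.

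The sample size arithmetic is correct, and its 80% is valid for CD4+ alone at unadjusted .05. The document gives no basis for the power of the other 11 to 12 measures. The main conclusion depends on which rule is applied, so this should be settled before group-level results are seen.

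**What to change.** 1. In Primary Outcome, name the CD4+ T-cell number as the single primary measure. Give it one pre-specified between-group contrast from the repeated-measures model. The average post-baseline difference is one reasonable choice, though the document does not imply a particular one.
2. Move the other cell numbers, PD-1 levels and NKG2D to secondary outcomes, tested with Holm or Benjamini-Hochberg.
3. In Sample Size Estimation, state that the 80% power applies to the CD4+ test only.

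**Cost.** No more patients are needed, because CD4+ is the measure on which the 64 per group was calculated. Choosing a different primary measure would remove that basis and need a new justification of the size. Recruitment began in September 2021 and the trial is registered and ethics-approved, so this is a mid-trial change to the primary outcome. It needs a dated amendment and a registry update, both made before group-level results are seen. The secondary markers will face stricter thresholds.
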